### Additional consent provisions for collection and use of participant data and biological specimens {26b}

The informed consent form includes a statement that all information obtained during the course of the trial will be regarded as confidential, that only the site trial team will be able to identify participants, that results will be published or presented in such a fashion that participants remain unidentifiable, and that hard copies of all participant records will be kept for 10 years in a locked facility at the trial site.

Consent for biological specimens is not applicable as no samples collected for HbA1c measurement will be stored.

## Interventions

### Explanation for choice of comparators {6b}

The comparator is standard of care diabetes management at each trial clinic (glucose monitoring) by participants assigned to Arm 3, their HbA1c levels and all the data collected from their case report forms (CRFs).

### Intervention description {11a}

The intervention is a CGM device (Abbot Freestyle Libre), which is considered low risk to trial participants as it is approved by the FDA, has the CE mark and is prescribed in both countries by private healthcare providers for the management of diabetes. It consists of a small interstitial fluid glucose sensor that is applied on the back of the upper arm, and a hand-held reader that collects glucose data when placed within 1.5 inches (4 cm) of the sensor. In the continuous CGM trial arm, participants will wear the CGM device all the time for the 9 months (replacing it every 2 weeks, concurrent with senor wear time). In the periodic CGM trial arm, participants will wear the CGM device for 2 weeks, scheduled to start 1 week before each clinic visit (except for the enrolment visit), and for 1 week after each clinic visit (except for the final follow-up visit).

### Criteria for discontinuing or modifying allocated interventions {11b}

A participant may discontinue CGM device use and be withdrawn for safety or administrative reasons at any time at the discretion of the Investigator. A participant may also decide to withdraw from the trial at any time. If a participant becomes pregnant, they will be permitted to remain in the trial to ensure external validity of the data.

### Strategies to improve adherence to interventions {11c}

An education session on the use of the CGM device will be provided for each participant during the enrolment visit (Day 1), which will be conducted by a qualified instructor and include guidance on how to self-apply the device, how to correctly interpret the information collected by the device, diabetes health and management, and awareness and management of potential adverse events. In addition, all clinicians (including registrars, nurse educators and research assistants) involved in the trial will receive an education package on clinical management and use of the CGM device.

### Relevant concomitant care permitted or prohibited during the trial {11d}

As this is a pragmatic trial embedded in routine clinical care, participants will be permitted to receive any concomitant care as clinically required. Potential confounding treatments will be assessed in a ‘Medical events and medical resources’ survey and include acetaminophen, ascorbic acid, intravenous vitamin C, sulphonamide antibiotics, and oxygen therapy, among others.

### Provisions for post-trial care {30}

As standard of care diabetes treatment is permitted during the studies, this will be continued once the trial has been completed. Any decision on whether to use a CGM device after the trial sits entirely with the participant and their attending clinician.

### Outcomes {12}

#### Primary outcome

The primary endpoint will be the mean change from baseline (pre-CGM device use) HbA1c at various timepoints up to 15 months (percentage and mmol/mol). This will be assessed in all trial arms and presented as absolute values and percentage changes, together with summary statistics and statistical comparisons (between group).

#### Secondary outcomes

Unless otherwise stated, the secondary outcomes listed below will be presented using descriptive statistics (i.e., means, standard deviations) or as intervention effects with 95% CI.CGM device outputs: (i) Coefficient of variation (%CV) for glucose levels; (ii–iv) the time spent ‘in-range’, below-range’, and ‘above range’ (percentage per day and absolute values [hours/minutes]).Number of hospitalisations due to diabetes complications.Health-related quality of life (HRQoL): (i) mean change from baseline in EQ-5D-Y/EQ-5D/EQ-5D-interviewer-administration scores [18–20]; (ii) mean change from baseline in type 1 diabetes distress (T1D-DDS) scores for participant and parent (where possible) [21]; (iii) qualitative assessment using focus group discussions with participants and caregivers.Adherence to CGM device use: the proportion of scheduled time registered using the CGM device (automatic device output).Acceptability: (i) mean change from baseline in Glucose Monitoring Satisfaction Survey for T1D (GMSS-T1D) score; [22] (ii) qualitative assessment using semi-structured interviews with healthcare providers and focus group discussions with participants.Cost: surveys will capture both direct and indirect costs of diabetes care at follow-up Visits 3 to 6 for trial participants, their caregivers (if possible), and healthcare providers. Incremental cost-effectiveness ratios (ICERs) and quality adjusted life years (QALYs) will be used for between-group comparisons.

#### Exploratory outcomes

In Kenya, the accuracy of the HbA1c point-of-care device used at each participating clinic will be assessed using a laboratory-based HbA1c method as reference. Mean relative bias, 95% limits of agreement and regression estimates will be presented. In South Africa, there are no exploratory outcomes, HbA1c test results analysed for the trial will be the ones used as per routine care.

#### Safety outcomes

Safety will be assessed by the recording of adverse events (AEs) and serious adverse events (SAEs) occurring during the trial period, as defined by the Common Terminology Criteria for Adverse Events (CTCAE). Given the pragmatic nature of the studies, reporting will be limited to SAEs. All events of grade 3 or above will be considered an SAE.

### Participant timelines {13}

The duration for each participant will be 15 months, consisting of 9 months of intervention followed by 6 months’ follow-up. There will be six scheduled trial visits in total, at Day 1, Visit 2 (Week 1), and at 3 (Week 11/12), 6 (Week 23/24), 9 (Week 35/36), and 15 months (Week 57/58); Fig. 1).

**Fig. 1 Fig1:**
[figure not shown]
Study timeline schematic. *Enrolment is expected to take from 3 to 8 months. Q, quarter

### Sample size {14}

Assuming a change in HbA1c levels of 2% after continuous use of a CGM device (determined by expert consultation) and an effect size of 0.2, a sample size of 246 participants (82 in each arm) would be required to achieve 80% power to detect within- and between-group differences at the 5% significance level (using repeated measures analysis of variance [ANOVA]).

For qualitative assessments, sample sizes will be pragmatically derived and will vary based on the number of available respondents and attainment of information/thematic saturation. In Kenya, the target populations will be 30 for focus group discussions and HRQoL surveys (10 in each arm) and 10 for semi-structured healthcare provider interviews. In South Africa, the target populations will be 45 for focus group discussions and HRQoL surveys (15 in each arm) and 10 for semi-structured healthcare provider interviews.

### Recruitment {15}

Recruitment will be staggered over a period of 4 weeks or until the target sample size has been reached. Participants will be recruited using purposive sampling at each of the sites, based on eligibility criteria. To raise awareness of the studies, recruitment flyers, which will contain basic trial information (purpose, inclusion criteria), as well as the contact details for the Principal Investigator and/or trial staff will be distributed to potential participants. Trial staff will contact eligible participants via phone and invite them to an information session at the clinic, or consecutively explain study procedures at their routine clinic visit. At that visit eligibility screening and informed consent/assent will take place. Reasons for refusal to participate will be recorded in the screening and enrolment logs and reviewed regularly by trial staff, so that strategies to maximise recruitment can be developed (if required).

The caregiver of every child or adolescent enrolled will be invited to participate in the HRQoL surveys and will be considered for inclusion in the focus group discussions. Parents of children under 8 years of age will also be asked to complete the surveys. All healthcare providers involved in the trial will be invited in person or via phone/email to take part in the semi-structured acceptability discussions.

## Assignment of interventions: allocation

### Sequence generation {16a}

Upon enrolment, each participant will be assigned a unique randomisation number in ascending numerical order, which determines their assignment to one of the three arms (1:1:1) according to the randomisation schedules generated prior to the trial by the FIND trial statistician. As this is an open-label trial, in order to minimise the risk of bias research assistants will be required to log into an electronic database (OpenClinica), where they will enter the participant’s unique randomisation number and the system will then inform them of the participant’s arm.

### Concealment mechanism {16b}

Only the trial statistician who generated the allocation sequences will have access to the allocation sequences.

### Implementation {16c}

As detailed in ‘Sequence generation {16a}’ section, the allocation sequences will be generated prior to trial initiation by the FIND trial statisticians. Trial Investigators/staff will enrol participants into the trial and assign them their randomisation numbers, which will determine their trial group based on the allocation sequences.

## Assignment of interventions: blinding

### Who will be blinded {17a}

As pragmatic, open-label trial, no blinding will be required.

### Procedure for unblinding if needed {17b}

As this will be open-label trial, unblinding will not be required.

## Data collection and management

### Plans for assessment and collection of outcomes {18a}

Trial outcomes are defined in the ‘Outcomes {12}’ section. All outcomes data relating to glucose levels will be extracted directly from the CGM device, as will data on adherence to CGM device use. However, in order to minimise bias in the intervention effect assessment, source data verification (from direct laboratory reports) will be implemented for the primary outcome measure (HbA1c). Other assessments will take place at the trial visits and timepoints outline in Table 1 and Table 2. Focus group discussions (~ 1 h) and semi-structured interviews (~ 1 h) will be conducted by trained staff at the Month 9 visit.

**Table 1 Tab1:** Schedule of assessments (Kenya study; NCT05944731)

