#### Objectives

The primary objective is to evaluate the impact of continuous and periodic CGM on changes to HbA1c levels in people with T1D in South Africa and Kenya, compared with standard of care.

Secondary objectives are as follows (versus standard of care where appropriate):To evaluate the impact of continuous or periodic CGM device use on glucose variability.To evaluate the impact of continuous or periodic CGM device use on the number of unplanned visits to outpatient clinics and/or hospitals as a result of diabetes complications.To evaluate the acceptability and feasibility of continuous or periodic CGM device use from the perspective of the participant, caregiver, and healthcare provider.To evaluate the cost of continuous or periodic CGM device use from a user and provider perspective.

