**ASSESSMENTS**							
Doctors visit (medical chart review)			All	All	All	All	All
HbA1c assessment			All	All	All	All	All
Medical events and resources survey				All	All	All	All
GMSS		All			All		All
HRQoL assessments		All				All	All
DDS		All			All	All	All
Acceptability questionnaire					Arms 1 and 2		Arms 1 and 2
Focus group discussion^c^						All	

*CGM* Continuous glucose monitoring, *DDS* Diabetes distress score, *GMSS* Glucose Monitoring Satisfaction Survey, *HRQoL* Health Related Quality of Life

^a^Includes identification of potential participants to be invited to the screening and enrolment day

^b^In the continuous CGM arm, the device is applied on on Day 1 and used until Month 9, for the periodic arm, a new device is provided at the visits shown and used for 1 week before each clinic visit (except for the enrolment visit), and for 1 week after each clinic visit (except for the final follow-up visit)

^c^Performed in a subset of participants

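### After baseline, participant acceptability is measured only at scheduled visits, so the earliest leavers give no data and GMSS scores from later leavers can be dropped

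*Protocol article*

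**What the plan says.** The second-to-last secondary objective in Objectives {7} is: "To evaluate the acceptability and feasibility of continuous or periodic CGM device use from the perspective of the participant, caregiver, and healthcare provider". Under Secondary outcomes, acceptability has two parts: "mean change from baseline in Glucose Monitoring Satisfaction Survey for T1D (GMSS-T1D) score", and "qualitative assessment using semi-structured interviews with healthcare providers and focus group discussions with participants".

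Timing is fixed in Plans for assessment and collection of outcomes {18a}: "Focus group discussions (~ 1 h) and semi-structured interviews (~ 1 h) will be conducted by trained staff at the Month 9 visit". The same section refers the other assessments to the visits in Tables 1 and 2. Those tables also carry a row called "Acceptability questionnaire", given to Arms 1 and 2 only.

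On leaving, Criteria for discontinuing or modifying allocated interventions {11b} says: "A participant may discontinue CGM device use and be withdrawn for safety or administrative reasons at any time at the discretion of the Investigator". It then adds: "A participant may also decide to withdraw from the trial at any time". No assessment is attached to either event, and neither table has a column for one.

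On analysis, Statistical methods {20a} limits GMSS to the Fully Complied or Partly Complied populations. Partly Complied requires, as a minimum, HbA1c values at Visits 1 and 5. Visit 5 is Month 9.

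**The concern.** Giving up a device and leaving the trial may itself be a sign that the device was not acceptable. If so, the acceptability data are missing for a reason tied to the outcome, and the reported result leans towards people for whom CGM worked well enough to stay. The article says the results are meant to inform policy in South Africa and Kenya. Readers there would want to know why people gave up, as well as how satisfied the rest were.

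There are two separate losses. One is at collection: some participants leave before any post-baseline question is put to them. The other is at analysis: GMSS scores already in the database from later leavers are excluded by the population definitions.

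**Working it through.** The article states no figure for acceptability, dropout or early stopping, so there is nothing to reproduce. The check sets the schedules against the population definitions and then gives a labelled illustration.

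**Step 1. When participants are asked (Tables 1 and 2).**

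| Measure | Kenya | South Africa |
|---|---|---|
| GMSS, all arms | Day 1, Months 3, 6, 9, 15 | Day 1, Months 6, 15 |
| Acceptability questionnaire, Arms 1 and 2 | Months 3, 6, 9 | Months 6, 15 |
| Focus group, subset of all arms | Month 9 | Month 9 |

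The intervention lasts 9 months. In South Africa, Month 6 is therefore the only GMSS or questionnaire round after baseline and within the intervention period. Month 15 comes 15 − 9 = 6 months after it ends. Focus groups reach a subset: 30 people in Kenya (10 per arm) and 45 in South Africa (15 per arm).

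**Step 2. What a CGM-arm participant contributes, by time of leaving the trial.**

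| Leaves | Post-baseline scores collected | Eligible for focus group | In a GMSS analysis population |
|---|---|---|---|
| Before Month 3 (Kenya) or Month 6 (South Africa) | None | No | No |
| After that round, before Month 9 | One or two rounds (Kenya); one (South Africa) | No | No, as there is no Visit 5 HbA1c |
| After Month 9 | Yes | Yes | Yes, if HbA1c was recorded at Visits 1 and 5 |
| Stops CGM but keeps attending | Yes | Yes | Partly Complied, on the same HbA1c condition |

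The first row is the collection loss. The second row is the analysis loss, and a different analysis population would recover it.

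**Step 3. How large the bias could be.** Let *d* be the share of CGM-arm participants whose answers are missing, *S* the result in those analysed and *L* the result in those missing. Then

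overstatement = *S* − [(1 − *d*)*S* + *dL*] = *d*(*S* − *L*).

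The same expression holds for a mean GMSS change. For GMSS as the article plans to analyse it, *d* covers the first two rows of Step 2, so it is at least as large as the share lost at collection alone.

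All inputs here are assumptions. Take *S* = 85% finding CGM acceptable:

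| *d* | *L* = 20% | *L* = 50% | *L* = 85% |
|---|---|---|---|
| 5% | 0.05 × 65 = 3.25 points | 0.05 × 35 = 1.75 | 0 |
| 10% | 6.5 | 3.5 | 0 |
| 20% | 13.0 | 7.0 | 0 |
| 30% | 19.5 | 10.5 | 0 |

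A percentage finding CGM acceptable is not an outcome the article defines. The table shows only how the bias depends on the share missing and on how far leavers differ.

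**The case against.** The strongest reply is that the gap rests on silence. The Trial status section names three full protocols (Kenya, Pretoria, Cape Town) that are not shown, and a withdrawal form with a reason for stopping could well be in them. That stands as a caution about the exit form. It does not dispose of the point, because the article prints both assessment schedules, fixes the focus groups at Month 9 and defines the GMSS populations. Those are statements, and the losses in Step 2 follow from them.

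A reader might infer that everyone who gives up CGM is never asked, so that the objective is answered only by those who kept using it. The documents do not support that:

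- The tables assign assessments by arm, not by current device use, so someone who stops CGM but still attends is still assessed.
- Later leavers can already have one or more scores.
- Sites are to contact people who miss a visit and rebook it.
- Provider interviews (10 per country) do not depend on participants staying.

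These protections have limits. Rebooking missed visits is not described for people who have withdrawn, and providers cannot stand in for the participant perspective that the objective names. Device-recorded adherence would reveal non-use, but it is analysed only in the Intervention population, which is restricted to full compliers in the CGM arms.

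It is also fair to say that the article expects little missing data and that this is a secondary, partly qualitative objective. Both limit the importance of the point without removing it.

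**Conclusion.** The point holds in a limited form. Followed as written, the plan collects no post-baseline acceptability data from CGM-arm participants who leave before Month 3 in Kenya or Month 6 in South Africa. It takes no focus-group contribution from anyone who leaves before Month 9. It excludes from the GMSS analysis later leavers without a Visit 5 HbA1c, even where scores exist.

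Participant acceptability may therefore be overstated. The direction assumes that leavers found CGM less acceptable than stayers did. The size cannot be computed from the article: it is zero if the two groups do not differ, and under the assumed rates above it runs from about 2 to about 20 points. No single figure in that range should be quoted as the expected bias. For the GMSS comparison with standard of care, the net effect also depends on who leaves Arm 3.

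A reader might also conclude that no choice of analysis population could help. That is wrong for GMSS scores already collected, and right only for answers that were never requested. This is an inexpensive improvement to a secondary objective. It does not affect the primary outcome.

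**What to change.** 1. Add a footnote to Tables 1 and 2: when CGM is stopped or the participant withdraws, Arms 1 and 2 are offered the existing acceptability questionnaire and GMSS, with one voluntary item on the reason for stopping, by phone if needed. If the full country protocols already provide this, show it in the tables.
2. Within the existing targets of 30 and 45, keep some focus-group or individual interview places for people who stopped early, and do not tie those places to attending Month 9.
3. Analyse GMSS and acceptability in all assigned participants with any post-baseline response, and report by arm how many left before being asked.

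The cost is real but small. Items 1 and 2 need an amendment with ethics submission, sponsor approval and re-signing by the investigators, across three protocols, with recruitment already under way in South Africa according to Trial status. They also need brief extra contacts by site staff. Item 3 needs no new data. The correction will be partial, because some leavers will decline to answer.

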	**STUDY PERIOD**						
	**Before enrolment**	**Enrolment / allocation**	**Post allocation study visits**				**Final follow-up**
	Day 0	Day 1 (Visit 1)	Week 1 (Visit 2)	Month 3 (Visit 3)	Month 6 (Visit 4)	Month 9 (Visit 5)	Month 15 (Visit 6)
**ENROLMENT**							
Pre-screening^a^	All						
Screening		All					
Enrolment		All					
Informed consent		All					
Baseline demographics		All					
Education session		All	All	All	All	All	All
**INTERVENTION**							
CGM device application or distribution^b^		Arms 1 and 2	Arm 2	Arm 2	Arm 2	Arm 2	
**ASSESSMENTS**							
Doctors visit (medical chart review)			All	All	All	All	All
HbA1c assessment		All		All	All	All	All
Medical events and resources survey				All	All	All	All
GMSS		All		All	All	All	All
HRQoL assessments		All		All	All	All	All
DDS		All		All	All	All	All
Acceptability questionnaire				Arms 1 and 2	Arms 1 and 2	Arms 1 and 2	
Focus group discussion^c^						All	

*CGM* Continuous glucose monitoring, *DDS* Diabetes distress score, *GMSS* Glucose Monitoring Satisfaction Survey, *HRQoL* Health Related Quality of Life

^a^Includes identification of potential participants to be invited to the screening and enrolment day

^b^In the continuous CGM arm, the device is applied once on Day 1 and used until Month 9, for the periodic arm, a new device is provided at the visits shown and used for 1 week before each clinic visit (except for the enrolment visit), and for 1 week after each clinic visit (except for the final follow-up visit)

^c^Performed in a subset of participants

**Table 2 Tab2:** Schedule of assessments (South Africa study; NCT05944718)

	**STUDY PERIOD**						
	**Before enrolment**	**Enrolment / allocation**	**Post allocation study visits**				**Final follow-up**
	Day 0	Day 1 (Visit 1)	Week 1 (Visit 2)	Month 3 (Visit 3)	Month 6 (Visit 4)	Month 9 (Visit 5)	Month 15 (Visit 6)
**ENROLMENT**							
Pre-screening^a^	All						
Screening		All					
Enrolment		All					
Informed consent		All					
Baseline demographics		All					
Education session		All	All	All	All	All	All
**INTERVENTION**							
CGM device application or distribution^b^		Arms 1 and 2	Arm 2	Arm 2	Arm 2	Arm 2	
**ASSESSMENTS**							
Doctors visit (medical chart review)			All	All	All	All	All
HbA1c assessment			All	All	All	All	All
Medical events and resources survey				All	All	All	All
GMSS		All			All		All
HRQoL assessments		All				All	All
DDS		All			All	All	All
Acceptability questionnaire					Arms 1 and 2		Arms 1 and 2
Focus group discussion^c^						All	

*CGM* Continuous glucose monitoring, *DDS* Diabetes distress score, *GMSS* Glucose Monitoring Satisfaction Survey, *HRQoL* Health Related Quality of Life

^a^Includes identification of potential participants to be invited to the screening and enrolment day

^b^In the continuous CGM arm, the device is applied on on Day 1 and used until Month 9, for the periodic arm, a new device is provided at the visits shown and used for 1 week before each clinic visit (except for the enrolment visit), and for 1 week after each clinic visit (except for the final follow-up visit)

^c^Performed in a subset of participants

